### Eligibility criteria

Patients will be eligible for the trial if they fulfill the following criteria:

• Planned transthoracic oesophagectomy for oesophageal carcinoma at a participating centre.

• Men over 18 years old on the day of first dose of the investigational medicinal product (IMP).

• Women over the age of 55 or more than 2 years since menopause.

• Women of potential child bearing age (under 55 and less than two years since menopause) may be recruited provided they agree to use contraception during the pre-post-operative period (eight weeks).

• Ability to give written informed consent to participate in the study.

Patients fulfilling any of the criteria below will be excluded:

• Known intolerance of vitamin D.

• Known sarcoidosis, hyperparathyroidism, or nephrolithiasis.

• Known serum corrected calcium >2.65 mmol/L.

• Undergoing haemodialysis.

• Pregnant or breastfeeding.

• Patients with tuberculosis or lymphoma.

• Diagnosis of chronic obstructive pulmonary disease (COPD) with a forced expiratory volume in one second (FEV1) less than 50% predicted or resting oxygen saturations of less 92%.

### Power and sample size estimate

There are no direct data to predict the effect size of vitamin D replacement upon EVLWI. In our preliminary work with 50 patients, the patients with 25(OH)D_3_ concentrations less than 15 nmol/L had the greatest increases in EVLWI (+3.2 ml/kg, +27%) compared to those patients with less severe deficiency pre–postoperatively (+1.0 ml/kg, +10% *P* = 0.013) suggesting that severe vitamin D deficiency influences EVLWI. As a group, after undergoing oesophagectomy our patients have a mean post-operative EVLWI of 10.1 ml/kg and standard deviation of 2.9 ml/kg. For the study to be able to detect a change of 20% in EVLWI with a power of 80% we will require approximately 34 patients in each arm to reach the primary endpoint (*P* = 0.05). An additional six patients will be needed to allow for dropouts, such as open/close cases, unexpected deaths and other difficulties with data collection. Thus, we intend to recruit 40 patients to each arm of the study.

With 34 patients completing each arm of the study, based upon preliminary unpublished data from 50 oesophagectomy cases, this study would detect a treatment effect of vitamin D upon the PO_2_:FiO_2_ ratio postoperative (PO) of ± 8.16 (± 20%), PO plasma soluble intercellular adhesion molecule-1 (sICAM-1) of ± 16 ng/ml (± 32%), plasma C-reactive protein (CRP) ± 53 ng/ml (± 33%), PO plasma von Willebrand factor (vWF) ± 55% relative to control plasma (± 24.7% change), PO plasma high-mobility group box 1 (HMGB-1) 5.42 ng/ml (± 54%), PO plasma myeloperoxidase (MPO) 105 pg/ml (± 57%), PO plasma MMP-9 51 ng/ml (± 57%), and PO plasma surfactant protein-D (SP-D) 691 ng/ml (± 61%). All calculations assume 80% power at a two-tailed significance level of 0.05.

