Recent data have further implicated vitamin D in adaptive immunity because of its influence upon the differentiation of T cells between the regulatory T cell (T_reg_) and the pro-inflammatory T helper 17 (T_h_17) subsets [28-30]. T_h_17 cells are known to stimulate tissue inflammation and neutrophil chemotaxis, both of which are seen in ALI, predominantly by IL-17 production. It also appears that expression of markers of T_reg_ cells (Foxp3) or T_h_17 cells (IL-17) by T cells may not be stable and that there is a greater degree of plasticity in their differentiation than previously appreciated [29]. Recent evidence has further suggested T_reg_ cells are important in the resolution of experimental ALI. This suggests that local lung regulation of the balance between T_reg_ and T_h_17 cells may be a determinant of resolution/persistence of neutrophilic inflammation which is known to be associated with a poor prognosis in human ALI.

Although the above suggest a potentially beneficial effect of vitamin D, we must exercise some caution as some studies have shown potentially adverse effects of vitamin D. In low dose nasal LPS challenge, cellular inflammation is actually lower in vitamin D receptor deficient (VDR KO) mice due to toll-receptor hyporesponsiveness. In addition the chemotactic effects of LL-37 could in theory increase neutrophil recruitment to the lung; albeit in ALI, CXCL-8 and ENA-78 are the main chemokines driving neutrophil recruitment. More recently it has been shown that the plasma LL-37 concentration was decreased in vitamin D supplemented patients with tuberculosis, possibly representing a global suppressive effect of vitamin D supplementation on markers of acute phase response or an indirect response to enhanced microbial killing [14]. Despite these reservations, the predominant biological effects of vitamin D led us to hypothesise that vitamin D deficiency may be a risk factor for ALI, causing elevated inflammation which results in exaggerated epithelial damage in at risk, vitamin D deficient individuals.

The VINDALOO trial is a three centre randomised double blind, placebo-controlled trial aiming to define the safety and effectiveness of a single high dose of vitamin D in preventing ALI in a group of patients at high risk of developing the condition.

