### Secondary outcomes

The trial secondary outcomes are clinical markers indicative of lung injury: PaO_2_:FiO_2_ ratio, oxygenation index, development of lung injury/ARDS during the first 28 days, ventilator and organ failure free days, survival (28 and 90 day) and safety and tolerability of vitamin D supplementation.

Lung injury will be defined by the American European Consensus Conference definition [35] as the acute onset of: (1) bilateral infiltrates on the chest x-ray; (2) hypoxaemia with a PaO_2_:FiO_2_ ratio of <40 kPa; and (3) absence of clinical evidence of left atrial hypertension. Ventilator free days are defined in accordance with the ARDSnet criteria as the number of calendar days after initiating unassisted breathing to day 28 after randomisation, assuming a patient survives for at least 48 consecutive hours after initiating unassisted breathing [36]. Un-assisted breathing is defined as one of at least 48 consecutive hours of: (1) being extubated with face mask, nasal prong oxygen, or room air; (2) T-tube breathing; and (3) tracheostomy mask breathing, CPAP = 5 cm H_2_0 without pressure support of intermittent mandatory ventilation assistance.

Organ failure free days are defined in a similar manner to ventilator free days with an organ failure free day being a day without evidence of non-respiratory organ failure. Organ failure will be defined as a sequential organ failure assessment (SOFA) score of greater than three [37].

Plasma indices of endothelial and alveolar epithelial function/injury, plasma inflammatory response will be measured by ELISA. Plasma vitamin D status (25(OH)D_3_, 1,25(OH)_2_D_3_, VDBP) and calcium will be assessed peri-operatively (pre-drug dose, pre-operative, post-operative, day 1 and day 3) as well as EVLWI day 1 post-operatively (measured at 9 am on day 1).

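### The 20% EVLWI target, averaged over patients of any vitamin D status, is close to the whole pilot contrast and is unexplained; the stated unadjusted t-test leaves out pre-dose 25(OH)D, reported to predict the outcome

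*Protocol article*

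**What the plan says.** All references are to the Protocol article.

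- **Target and sample size (Power and sample size estimate).** The section first concedes that nothing directly predicts the effect of replacement on EVLWI. It then gives the target, "For the study to be able to detect a change of 20% in EVLWI with a power of 80"%, the inputs, "our patients have a mean post-operative EVLWI of 10.1 ml/kg and standard deviation of 2.9 ml/kg", and the result, "we will require approximately 34 patients in each arm to reach the primary endpoint". The level is confirmed at the end of the section: "All calculations assume 80% power at a two-tailed significance level of 0.05". Six more per arm for dropout gives 40.
- **Pilot evidence (same section).** Among 50 patients, those with 25(OH)D3 below 15 nmol/L had a pre-to-post rise of 3.2 ml/kg, against 1.0 ml/kg in those with less severe deficiency (P = 0.013). The authors read this as "suggesting that severe vitamin D deficiency influences EVLWI".
- **Hypothesis (background section on severe deficiency as a driver).** Deficiency is expected to cause inflammation leading to "exaggerated epithelial damage in at risk, vitamin D deficient individuals".
- **Entry (Eligibility criteria; Concomitant medications).** The disease criterion is "Planned transthoracic oesophagectomy for oesophageal carcinoma at a participating centre". No 25(OH)D threshold is set; the only related limit is on current supplement intake.
- **Measurement (Secondary outcomes).** Plasma vitamin D status "will be assessed peri-operatively (pre-drug dose, pre-operative, post-operative, day 1 and day 3"). The Primary outcome section adds that earlier work showed preoperative vitamin D status to influence lung water accumulation.
- **Analysis (Statistical analysis plan).** Described as a brief account, with a detailed plan to follow: independent-samples t-tests for continuous outcomes, after transformation if needed, or non-parametric equivalents.

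**The concern.** The evidence for an effect is a contrast between two levels of deficiency. The powered effect is an average over everyone having the operation, whatever their vitamin D status. If the benefit lies mostly in the severely deficient, the average is smaller than the pilot contrast in proportion to their share, and the section makes no allowance for this. The 80% would then describe an effect larger than the cited evidence implies for the enrolled population, and a neutral result could be over-read as evidence against benefit in severe deficiency.

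A second issue can be acted on directly. The article itself presents vitamin D status as a predictor of the primary outcome and schedules a pre-dose sample, yet the test it names for continuous outcomes uses no baseline information.

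**Working it through.** **Inputs** (Power and sample size estimate): mean 10.1 ml/kg; SD 2.9 ml/kg; target 20%; two-sided 0.05; power 80%; 34 evaluable per arm; pilot rises 3.2 and 1.0 ml/kg; P = 0.013 in 50 patients. The share f of patients below 15 nmol/L is not given. I assume 25% to 60%.

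**1. The plan's own figure.** Target Δ = 0.20 × 10.1 = 2.02 ml/kg.
n per arm = 2 × (1.96 + 0.8416)² × 2.9² / 2.02² = 32.4, so 33 by the normal approximation. The t-distribution gives 33.3, so 34. The stated 34 is reproduced. Standard error at 34 per arm = 2.9 × √(2/34) = 0.703. Power = Φ(2.02/0.703 − 1.96) = 82% (81% with the t-distribution).

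**2. Target against pilot contrast.** 3.2 − 1.0 = 2.2 ml/kg, and 2.02/2.2 = 92%. The pilot contrast is in change and the target is expressed on the post-operative mean. Under randomisation the expected between-arm difference is the same on either scale, so the comparison is fair, though the SD of change is not given.

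**3. Benefit confined to severe deficiency.** Assume the 2.2 ml/kg is fully reversed there and nothing happens elsewhere. Average effect = 2.2 × f; power = Φ(2.2f/0.703 − 1.96).

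| f (assumed) | Average effect, ml/kg | Power at 34 per arm |
|---|---|---|
| 25% | 0.55 | 12% |
| 30% | 0.66 | 15% |
| 40% | 0.88 | 24% |
| 50% | 1.10 | 35% |
| 60% | 1.32 | 47% |

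The t-distribution gives values within about one percentage point. An average of 2.02 needs f of about 92%.

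**4. Opposite extreme.** Assume treatment abolishes the whole pilot rise in every patient. Average effect = 1.0 + 2.2f: 1.55 ml/kg at f = 25% (power 60%) and 2.32 ml/kg at f = 60% (power 91%). It reaches 2.02 when f = (2.02 − 1.0)/2.2 = 46%.

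**5. What adjustment could gain.** If P = 0.013 came from a two-group t-test on 50 patients, t is about 2.58 on 48 degrees of freedom, and the share of variance in change explained is 2.58²/(2.58² + 48) = 12%. If the same share applied to the analysed outcome, the residual SD would be 2.9 × √(1 − 0.12) = 2.72 and the standard error 2.72 × √(2/34) = 0.66. Power at 2.02 ml/kg would rise from 82% to about 87%; the range in step 3 would move only from 12%–47% to about 13%–52%. This is optimistic: the pilot figure concerns change, and effective treatment would weaken the association in the treated arm.

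**6. Power of an interaction test.** Splitting at 15 nmol/L, with a true difference in effect of 2.2 ml/kg and n₁ = 34f rounded, the standard error is 2.9 × √(2/n₁ + 2/(34 − n₁)). At f = 25% (8 and 26 per arm) this is 1.66, giving Φ(2.2/1.66 − 1.96) = 26%. At f = 50% (17 and 17) it is 1.41, giving 35%. At f = 60% it is 34%.

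**The case against.** The strongest reply is that 20% is offered as a detectable difference, not a prediction. The section says openly that direct data are lacking and never derives 20% from the pilot contrast, and the Discussion presents the trial as proof of concept. Enrolling without a biomarker threshold is a legitimate choice. All of this stands.

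The pilot contrast is also not a ceiling. The comparison group was itself deficient and its EVLWI still rose by 1.0 ml/kg, so replacement might help there too. This stands, and it means the 92% requirement belongs to one scenario. It does not remove the concern: even with the rise abolished in everyone, 2.02 ml/kg is reached only if at least 46% are severely deficient.

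Two stronger readings are tempting and are not supported:

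- A reader might infer that a null result could not test the trial's hypothesis. The Abstract states the aim for patients having elective transthoracic oesophagectomy, and the randomised comparison tests exactly that. The sentence on deficient individuals is mechanistic rationale and is not limited to those below 15 nmol/L.
- A reader might infer that no analysis by baseline 25(OH)D is planned. The article gives its methods in brief and defers to a detailed plan that is not shown, so this cannot be established. What can be said is that the method named for continuous outcomes is unadjusted.

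Finally, adjustment and an interaction test do not restore power lost to dilution. Steps 5 and 6 confirm this, so they should not be presented as a cure.

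**Conclusion.** The point holds in limited form. The sample-size calculation is right for the difference it names, and the overall comparison answers the all-comer question. What is weak is the justification: the powered average effect is 92% of a contrast seen between severe and less severe deficiency, applied to an unselected population without explanation. If benefit is confined to severe deficiency, power is about 12% to 47%, and a null would be weak evidence about that group. That range rests on an assumed share of 25% to 60%, full reversal of 2.2 ml/kg in that group, no effect elsewhere, and SD 2.9 ml/kg. With benefit in everyone, power is much higher (60% to 91% in the extreme case).

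The improvement that can be made now concerns the analysis. By the article's own account, pre-dose 25(OH)D predicts lung water accumulation. It is already scheduled for collection, and adjusting for it is a better method than the t-test stated. The gain in precision is modest and uncertain.

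**What to change.** Keep the sample size and the entry criteria.

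1. In place of the unadjusted t-test, analyse the primary EVLWI outcome with a linear model for treatment adjusted for pre-dose 25(OH)D as a continuous covariate.
2. Pre-specify one treatment-by-baseline-25(OH)D interaction. Report treatment-effect estimates with confidence intervals below 15 nmol/L and above, labelled supportive and low-powered (about 26% to 35% for a split at 15 nmol/L under the assumptions above).
3. Optionally, note beside the 80% figure that a null overall result would not exclude benefit confined to severe deficiency.

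The detailed analysis plan, still to be written according to the article, is the natural place for items 1 and 2. The cost is some wording and one extra model on samples already scheduled. The downside is a supportive test with low power, which could itself be over-read if not labelled.

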### Trial conduct

#### Approach to patients and obtaining informed consent

Patients will be identified through upper gastrointestinal cancer teams. Eligible patients will be invited to participate by their treating clinician, specialist clinical nurse or research nurse. If agreeable, written informed consent will be obtained, following a face to face discussion about the study.

### Randomisation and drug / placebo supply

The trial drug manufacturer will produce the randomisation sequence using a block size of 10 with equal allocation between active and placebo groups. Drug (oral cholecalciferol oily solution Vigantol, 300,000 IU (7.5 mg)) and matching placebo (Miglyol 812 oil, the vehicle for vitamin D3 in Vigantol) will be supplied and packaged according to the randomisation sequence into numbered treatment boxes by Novalabs (Leicester, UK). Drug boxes will be supplied to centres in blocks of 10 thus ensuring an equal allocation between active and placebo groups to balance any differences in case mix, pre-operative, operative and post-operative care between centres. Patients will be randomised sequentially by allocating them to the next numbered treatment pack held at the centre.

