### Statistical analysis plan

Data will be analysed with the help of the trial statistician. Data will be analysed using SPSS for Windows 17.0. A detailed analysis plan will be developed during the trial prior to commencement of analysis. In brief, for continuously distributed data, differences between groups will be tested using independent samples t-tests with transformations of variables to Normality if appropriate, or non-parametric equivalents. Chi-squared tests (or Fisher’s Exact tests) will be used for categorical variables. A *P* value of 0.05 will be considered as significant. We will test for significant correlations between changes in the biological markers using standard methods. The treatment effect will be analysed on an intention-to-treat basis. For further examinations of relationships between a binary variable and known explanatory variables, the following tests will be applied as appropriate. Logistic regression will be used to provide the estimated risk ratios for the treatment effect with associated 95% confidence interval (CI). Time to event outcomes, such as duration of ventilation or duration of hospital stay, will be analysed by survival methods and reported as hazard ratios and 95% CI. A single final analysis is planned at the end of the trial.

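### Allocation is blocked within centre but the named tests omit centre: if centre affects EVLWI, the unadjusted t-test will be somewhat conservative and give up some precision

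*Protocol article*

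**What the plan says.** The section on randomisation and drug supply sets a block size of 10 with 1:1 allocation and states: "Drug boxes will be supplied to centres in blocks of 10 thus ensuring an equal allocation between active and placebo groups". The purpose given is "to balance any differences in case mix, pre-operative, operative and post-operative care between centres". Patients take the next numbered pack held at their own centre. The abstract gives three centres and 80 patients.

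For continuous outcomes, the section headed Statistical analysis plan states that "differences between groups will be tested using independent samples t-tests", after transformation if needed, or by non-parametric equivalents. Categorical outcomes get chi-squared or Fisher's exact tests. Regression on explanatory variables appears only as a further look at binary variables, and centre is not named. The section calls itself a brief account and says a detailed plan will be written before analysis begins.

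The sample size section uses a "mean post-operative EVLWI of 10.1 ml/kg and standard deviation of 2.9 ml/kg" and arrives at "approximately 34 patients in each arm to reach the primary endpoint".

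**The concern.** Because each centre works through its own blocks of 10, the arms are close to equal in size within every centre. A difference in mean EVLWI between centres therefore largely cancels out of the comparison of arms. The two-sample t-test does not use this: its pooled variance still contains the between-centre part. If that part is not zero, the standard error is too large, the confidence interval is too wide and the true type I error falls below the nominal 5%. The design would buy precision that the named analysis does not collect.

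At stake is efficiency, not validity. The primary endpoint is sized with little to spare, so precision that can be had for two degrees of freedom is worth taking.

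**Working it through.** **Inputs from the protocol article.** Mean 10.1 and SD 2.9 ml/kg; a 20% change, so 0.20 × 10.1 = 2.02 ml/kg; 34 evaluable patients per arm. On error rates: "All calculations assume 80% power at a two-tailed significance level of 0.05".

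**Reproducing the planned size.** Normal approximation: n = 2 × (1.960 + 0.842)² × 2.9² / 2.02² = 32.4, so 33 per arm. The t-distribution gives 33.3, so 34, as stated. Power at 34 per arm is 81.9% (normal) or 80.8% (t). Adding 6 per arm for dropout gives 40.

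**Assumption.** Let ρ be the share of total EVLWI variance that lies between centres. The article gives no value, so a range is shown. The formulas also assume arms balanced within centre and the same treatment effect in every centre.

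**Formulas, total SD held at 2.9.** The standard error used by the t-test is SE = 2.9 × √(2/34) = 0.703, so 2.02/SE = 2.872. The true standard error of the contrast is SE × √(1−ρ). Hence:

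- true type I error of the t-test = 2 × [1 − Φ(1.96/√(1−ρ))]
- power of the t-test = Φ[(2.872 − 1.96)/√(1−ρ)]
- power with a centre term = Φ[2.872/√(1−ρ) − 1.96]
- excess width of the confidence interval = 1/√(1−ρ) − 1

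Example at ρ = 0.10, where √0.90 = 0.949: the type I error uses 1.96/0.949 = 2.066, giving 3.9%; t-test power is Φ(0.961) = 83.2%; adjusted power is Φ(1.067) = 85.7%.

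| Assumed ρ | True alpha, t-test | Power, t-test | Power with centre | Loss (points) | Interval too wide by |
|---|---|---|---|---|---|
| 0 | 5.0% | 81.9% | 81.9% | 0 | 0% |
| 0.02 | 4.8% | 82.2% | 82.7% | 0.5 | 1% |
| 0.05 | 4.4% | 82.5% | 83.8% | 1.3 | 3% |
| 0.10 | 3.9% | 83.2% | 85.7% | 2.5 | 5% |
| 0.20 | 2.8% | 84.6% | 89.5% | 4.9 | 12% |

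**Check by simulation.** There were 10,000 trials per setting, with permuted blocks of 10 including incomplete ones, and assumed centre sizes of 30/20/18 and 48/12/8. The type I error of the t-test was 4.4% to 4.5% at ρ = 0.05, 3.8% to 4.3% at 0.10 and 3.1% at 0.20; with a centre term it stayed near 5%. The power loss was about 1, 3 and 6 points at those shares. Unadjusted power stayed at or above 80% in every setting.

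**If 2.9 is instead a within-centre SD.** The article does not say which it is. The total SD is then 2.9/√(1−ρ). Adjusted power stays at 81.9%, and t-test power becomes Φ[(2.872 × √(1−ρ) − 1.96)/√(1−ρ)]: about 80.5% at ρ = 0.05, 79.0% at 0.10 and 75.2% at 0.20.

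**The case against.** The best defence is that the analysis section is an explicit summary. A detailed plan is promised, and it could add centre without contradicting anything in the article. That is true, and it makes correction easy. It does not remove the point, because the summary already names a test, and a plan that followed it literally would omit the blocking factor.

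Three further objections stand and limit what can be claimed.

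- A reader might infer that the centres do differ. The text speaks of balancing "any" differences, which is a precaution. It does not report that centres differ, still less that EVLWI does.
- A reader might infer that P values and intervals will be too conservative and power will be lost. That follows only if centre predicts outcome. No between-centre variance or centre size is stated. At a zero share nothing is lost, and at 5% or below the loss is about one point or less (1.3 by the closed form at 5%).
- A reader might extend the loss to the chi-squared and Fisher's exact tests. The calculations cover a continuous outcome only, so no figure supports a loss for any binary outcome.

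**Conclusion.** The mismatch holds: allocation is restricted by centre, and the tests named for continuous outcomes leave centre out. The direction is also clear: if centre affects EVLWI, the unadjusted t-test is conservative. The size is conditional on an assumed centre share. It is trivial up to about 5% of the variance, and about 2.5 to 5 power points between 10% and 20%.

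It would be wrong to read this as a threat to validity or to the planned power in general. Type I error is not inflated. If 2.9 ml/kg is the total SD, the planned 80% is met throughout the range examined, and what is given up is power above the target. Only if 2.9 is a within-centre SD does the unadjusted analysis fall short, to about 79% at a 10% share and 75% at 20%. Priority is minor to moderate: a low-cost improvement, best settled before analysis begins.

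**What to change.** Replace the independent-samples t-test for EVLWI and the other continuous outcomes with a linear model containing treatment and centre (two indicator terms for three centres), fitted on the transformed scale where needed. Report the treatment effect with its 95% confidence interval from that model.

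For binary outcomes, a centre-stratified analysis such as Mantel-Haenszel is optional where event numbers allow.

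The cost is one sentence in the detailed analysis plan and two degrees of freedom: with 68 evaluable patients, residual degrees of freedom go from 66 to 64. If centre turns out not to matter, almost nothing is lost.
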